##### Acceptability

Percentage of responses observed in agree or strongly agree to each of the four Likert-scale items designed to assess acceptability will be calculated at wave *W*, where *W* = W1 or W2 or W3. The lower bound threshold is < 60%. The upper bound threshold is ≥ 80%.

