Consistent with previous research [34], a brief cover letter, written and pictorial wear instructions, a daily log sheet regarding wear time, protocol checklist, and one preaddressed postage-paid, padded, return envelope (regular USA mail) will be included in the PAMP. In the cover letter, participants will also be directed to use their login credential to access electronic copies of the paper-based documents in the PAMP. Wear instructions will include the following: ensure that the belt is snug around the waist and that monitors are placed over the right hipbone crest at the anterior axillary line during wear time; begin to wear the monitors upon awakening the day after receipt for a seven-day interval; remove the monitors when sleeping or during water intensive activities (e.g., swimming, bathing) and reattach the monitors upon awakening or at cessation of water intensive activities; complete the daily log sheet online with date and time the monitors are put on and taken off each day; and return the monitors and belt on the day after a 7-day interval via the preaddressed postage-paid, padded, return envelope provided. On the day after a 7-day interval, participants will receive a reminder by e-mail and/or phone to return the belt and the monitors. At this time, participants will also be prompted to complete instruments designed to measure the acceptability of accelerometer-based assessment of physical activity and self-reported physical activity.

Upon return of the belt and the monitors the research team will follow a protocol based on previous research [34]. Data will be downloaded using a standard universal serial bus port. Belts will be laundered. Batteries in the monitors will be charged or changed if necessary. Monitors will be reinitialized for use. Within a few weeks of the return of the monitors, participants who provide usable data (to be described in the section on the ActiGraph wGT3X-BT) will be e-mailed (or mailed via regular mail if an e-mail address is unavailable) a preliminary estimate of their wear time and average minutes per day of MVPA in relation to broad categories of recommended MVPA per week (i.e., 0–4.21 min/day = minimal; 4.21–21.36 min/day = less than recommended; ≥ 21.36 min/day = meeting recommendation of 150 min/week). Participants who do not provide usable data will be informed that their average minutes per day of MVPA cannot be estimated due to insufficient data.

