##### Participation rates

Participation rate at wave *W*, where *W* = W1 or W2 or W3, will be defined as the percentage of consented patients who provide usable data at wave *W*: (*n*_usable data at wave *W*_/*n*_consent_) × 100. The lower bound threshold is < 50%. The upper bound threshold is ≥ 70%.

The definition of usable data will follow the description previously provided in the *ActiGraph wGT3X-BT* section.

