##### Acceptability: quantitative

Percentage of responses observed in “yes” to the following item—“Would you be willing to wear the belt again as a part of a new research study?” will be calculated at wave *W*, where *W* = W1 or W2 or W3. The lower bound threshold is < 75%. The upper bound threshold is ≥ 85%.

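### The acceptability and wear-again lights count only the answers received at each wave, so belt-related non-response could turn them green with no change in opinion

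*Protocol article*

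**What the plan says.** Under Data analysis, Aim 1, Acceptability, the indicator is the "Percentage of responses observed in agree or strongly agree to each of the four Likert-scale items", calculated separately at W1, W2 and W3. It is red below 60% and green from 80%.

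Under Aim 3, Acceptability: quantitative, the item "Would you be willing to wear the belt again as a part of a new research study" is scored with the same opening words, "Percentage of responses observed in", applied to the answer yes. It is red below 75% and green from 85%. Neither section says how a participant who gives no answer counts.

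The participation rate, in the same Aim 1, is the "percentage of consented patients who provide usable data at wave" in question, divided by the number consented; it is red below 50% and green from 70%. The retention rate has the same denominator and is red below 40% and green from 60%.

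On timing, the section on W1, W2 and W3 physical activity monitoring says that on the day after each 7-day interval "participants will also be prompted to complete instruments designed to measure the acceptability of accelerometer-based assessment of physical activity".

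The opening of Data analysis reads each indicator against its own two thresholds and treats a value above the upper one as support for a definitive trial. It also states a missing-at-random assumption with the software's default handling.

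**The concern.** Both opinion indicators are conditional on answering. The questions come after a week of wearing the belt, at three successive waves. A participant who has given up on the belt may well be less likely to answer, and the gift card at each wave depends on completed monitoring as well as the survey battery (Usual care; Fun For Wellness). If non-response is concentrated among those who dislike the belt, the remaining responders become more favourable from wave to wave without any change in opinion.

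The general missing-data statement does not help. The two sections specify raw percentages of observed answers, not model-based estimates, and an answer withheld because of the opinion itself is not missing at random unless observed data explain it.

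At stake are the W2 and W3 lights for whether (Aim 1) and how (Aim 3) belt-worn accelerometry can be used. A green light that describes only the willing responders could be carried into the planning of the definitive trial as a statement about everyone who consented.

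**Working it through.** **Inputs.** 30 consented is the enrolment target (Sample size). The thresholds are those given above and in Table 2. The article gives no expected acceptability, questionnaire response rate or reason for loss, so there is no figure of the plan's own to reproduce, and every response pattern below is an assumption.

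**Step 1: opinions fixed, only unfavourable participants lost.** Observed percentage = favourable / (30 − lost).

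| Item | All 30 answer | Lost | Responders only |
|---|---|---|---|
| Acceptability | 17/30 = 56.7%, red | 9 | 17/21 = 81.0%, green |
| Acceptability | 18/30 = 60.0%, yellow | 8 | 18/22 = 81.8%, green |
| Wear-again | 20/30 = 66.7%, red | 7 | 20/23 = 87.0%, green |

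**Step 2: less extreme loss.** Let p be the true favourable share, a the response rate among favourable participants and u the response rate among the others. Expected observed share = p·a / [p·a + (1 − p)·u]. With p = 0.65 (yellow):

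- a = 0.80, u = 0.30: 0.520 / (0.520 + 0.105) = 83.2%, green
- a = 0.80, u = 0.40: 0.520 / (0.520 + 0.140) = 78.8%, just under green
- a = 0.80, u = 0.60: 0.520 / (0.520 + 0.210) = 71.2%, yellow
- a = 0.60, u = 0.60: 0.390 / (0.390 + 0.210) = 65.0%, no drift

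The shift therefore depends on the difference between a and u, not on the amount of loss alone.

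**Step 3: do the other lights catch it?** Participation is green at 70% of 30 = 21, and retention at 60% of 30 = 18. Suppose, as an assumption, that exactly those with usable data answer. The smallest green counts among responders, and the same counts over all consented, are:

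| Responders | Acceptability, responders | Over 30 | Wear-again, responders | Over 30 |
|---|---|---|---|---|
| 27 | 22/27 = 81.5% | 73.3% | 23/27 = 85.2% | 76.7% |
| 21 | 17/21 = 81.0% | 56.7% | 18/21 = 85.7% | 60.0% |
| 18 | 15/18 = 83.3% | 50.0% | 16/18 = 88.9% | 53.3% |

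At 21 responders, participation, retention, acceptability and wear-again can all be green while the favourable answers cover 56.7% and 60.0% of those consented. The figures over 30 count every non-responder as unfavourable, so they are lower bounds and not estimates.

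**Step 4: could the existing thresholds simply be applied to all consented?** With 21 responders and unanimous willingness, 21/30 = 70%, which is below the wear-again lower threshold of 75%. A rule that required the all-consented figure to clear that threshold would make green impossible at a response rate that participation itself calls green.

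**The case against.** The strongest reply is that opinion among responders and loss of participants are different quantities, and that the plan scores both. Participation and retention have their own lights over the number consented, and the indicators are not merged into one score. That stands. A reader might infer that a protocol which drives away its unhappy participants scores better overall. The article does not support this, because such a protocol would do worse on participation and retention. What remains is that those lights measure usable ActiGraph data rather than questionnaire response, tolerate 30% and 40% loss while green, and are not tied to the opinion lights by any rule.

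A reader might also infer that the lights must drift green as participants are lost. They need not: equal response leaves 65% at 65%, and nothing in the article shows that loss will be belt-related.

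Nor is questionnaire response the same as retention. Usable data require a log sheet with a valid start date, at least four days of ten hours including a weekend day, and no monitor error. A participant can fail that test and still answer the prompt, which is not made conditional on wear. Response may therefore exceed 60% or 70%. The W1 questionnaire also precedes later loss and can record early dissatisfaction, and the local setting allows staff to follow up.

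Finally, different denominators for different constructs are not a contradiction, and an article leaves reporting detail to the full plan. The scoring rule for these lights, however, is fixed in the article itself, and it is that rule which can mislead.

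**Conclusion.** The point holds in conditional form. Both opinion indicators are percentages of answers received, and no stated rule shows whether a green W2 or W3 light reflects acceptance or selective response. If loss falls on those who dislike the belt, a light can move from red to green with opinions unchanged: losing 9 of 30 is enough for acceptability at 17 favourable, and losing 7 of 30 for wear-again at 20 favourable. With partial selectivity the shift is smaller, for example from 65% to between 71.2% and 83.2% under the unequal response rates tried. With none it is zero.

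These results rest on 30 consented and on assumed response patterns. W2 and W3 are the most exposed. The thresholds need not be moved; the lights need enough beside them to show how far non-response could have carried them.

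**What to change.** Amend Acceptability (Aim 1) and Acceptability: quantitative (Aim 3), with a note to Table 2:

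1. For each item and wave, report the number responding, the percentage of responders, and the percentage of all consented with non-response counted as not favourable. Label the last a lower bound.
2. For participants lost by W2 or W3, report their W1 or last available answers to the same items.
3. Keep the light on the responder percentage. Where the two percentages fall in different colours, flag the light as sensitive to non-response and do not read it as unqualified support.

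Do not make the existing thresholds over all consented a condition for green, for the reason in Step 4.

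The cost is a few sentences and extra table columns; the data are already to be collected. The downside is that the lower bound is conservative, since some non-response has nothing to do with the belt. With 30 participants the flag will also appear readily near a cut-off: 22/27 is green among responders and 22/30 yellow. It should therefore be read as a caution and not as a downgrade.

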##### Recruitment rate

Recruitment rate will be defined as the percentage of patients who select “yes” when asked if they are interested in determining if they are eligible for participation in this study: (*n*_interested_/[*n*_interested_ + *n*_no_ + *n*_defer_]) × 100. The lower bound threshold is < 40%. The upper bound threshold is ≥ 60%.

##### Eligibility rate

Eligibility rate will be defined as the percentage of interested patients who are presented with the informed consent form: (*n*_eligible_/*n*_interested_) × 100. The lower bound threshold is < 60%. The upper bound threshold is ≥ 80%.

##### Consent rate

Consent rate will be defined as the percentage of eligible patients who consent to participate in this study: (*n*_consent_/*n*_eligible_) × 100. The lower bound threshold is < 80%. The upper bound threshold is ≥ 90%.

##### Participation rates

Participation rate at wave *W*, where *W* = W1 or W2 or W3, will be defined as the percentage of consented patients who provide usable data at wave *W*: (*n*_usable data at wave *W*_/*n*_consent_) × 100. The lower bound threshold is < 50%. The upper bound threshold is ≥ 70%.

The definition of usable data will follow the description previously provided in the *ActiGraph wGT3X-BT* section.

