### Proposed study

The feasibility study proposed in this paper will be the first study to use accelerometry within the FFW online behavioral intervention. The objective of this manuscript is to describe the protocol for a feasibility study designed to address uncertainties regarding the inclusion of accelerometer-based assessment of free-living physical activity within the FFW online intervention among adults with obesity in the USA. Four specific aims will be investigated.

#### Aim 1

To determine if accelerometer-based assessment of physical activity *can* be used within the FFW intervention.

#### Aim 2

To determine if accelerometer-based assessment of physical activity *should* be used within the FFW intervention.

#### Aim 3

To determine *how* to implement accelerometer-based assessment of physical activity within the FFW intervention. Aim 3 assumes a positive response to Aim 2.

#### Aim 4

To provide a preliminary effect size estimate for each direct effect depicted in the conceptual model (see Fig. 2) for the FFW online intervention (e.g., FFW → Physical Activity).

Pursuit of these four specific aims is based on a general conceptual framework for feasibility and pilot studies in preparation for a future definitive RCT [42–44]. Within this conceptual framework, a randomized pilot trial is a type of a feasibility study and a feasibility study may include a focus on the acceptability of an intervention [42–44].

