### Sample size

Thirty participants will be targeted for enrollment in this study. There are three rationales for the target sample size. First, the target sample size fits well within the range of sample sizes often observed in pilot and feasibility trials [45]. Second, and with regard to aim 1 through aim 3 of this study, the target sample size is consistent with sample sizes observed in similar research [31, 46–48]. Third, and with regard to Aim 4 of this study, the target sample size is based on budgetary constraints and not a sample size determination for a desired level of statistical power [42–44]. Budgetary constraints preclude enrollment of more than 30 participants in this study.

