#### Usual care

Participants assigned to the UC group (i.e., UC participants) will proceed through the preoperative weight management program provided by the center. The login credential for each UC participant will, however, provide access to a secure website to complete data collection (i.e., a survey battery and physical activity monitoring) at W1, W2, and W3. UC participants will have the opportunity to receive up to $30 worth of Amazon electronic gift cards, which is similar to previous research [36, 37]. Specifically, UC participants will receive $10 for completing the W1 survey battery and W1 physical activity monitoring, $10 for completing the W2 survey battery and W2 physical activity monitoring, and $10 for completing the W3 survey battery and W3 physical activity monitoring. UC participants will be given 4 weeks of 24 h access to the FFW online intervention approximately 1 month after data collection for this study is closed.

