##### Retention rates

Retention rate through wave *W*, where *W* = W2 or W3, will be defined as the percentage of consented patients who provide usable data at W1 through wave *W*: (*n*_usable data through wave W_/*n*_consent_) × 100. The lower bound threshold is < 40%. The upper bound threshold is ≥ 60%. The definition of usable data will follow the description previously provided in the *ActiGraph wGT3X-BT* section.

#### Aim 2

Pearson’s correlation coefficient and Bland-Altman analyses will be used to determine if accelerometer-based assessment of physical activity *should* be used within the FFW intervention. Threshold values for the traffic light system for the specific indicators that will be used to evaluate aim 2 are based on inferences drawn from the results of previous research [47, 48].

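### The W2 and W3 participation and retention lights pool both arms, so they can be green while the FFW arm, which Aim 1 is about, is red on the plan's own scale

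*Protocol article*

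**What the plan says.** Under Proposed study, Aim 1 is to find out whether accelerometer-based assessment can "be used within the FFW intervention". Two of its indicators are defined under Data analysis, Aim 1:

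- Participation rate: the "percentage of consented patients who provide usable data at wave" W1, W2 or W3. Red is below 50%, green is 70% or more.
- Retention rate: the "percentage of consented patients who provide usable data at W1 through wave" W2 or W3. Red is below 40%, green is 60% or more.

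Both formulas divide by the number consented. Table 2 gives one pair of thresholds per indicator, and no rate or light by arm is stated.

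Other sections fix who is in that denominator:

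- Sample size: "Thirty participants will be targeted for enrollment in this study". Randomization sets 15 per arm.
- Informed consent, Wave (W) 1 survey battery and Randomization: allocation follows consent and the W1 survey.
- Usual care: "Participants assigned to the UC group (i.e., UC participants) will proceed through the preoperative weight management program provided by the center". These participants are offered FFW only about a month after data collection closes.
- Study timeline: W1 monitoring is in week 2, FFW access in weeks 3 to 6, and W2 and W3 monitoring in weeks 8 and 12.

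**The concern.** At W2 and W3 about half of the people behind each light have never had access to the intervention that Aim 1 names. The pooled rate is the average of the two arms, so high compliance in UC can offset poor compliance in FFW. A green light could then be taken as support for accelerometry inside FFW, and for the definitive trial, when the FFW arm alone would have been red.

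A between-arm gap in usable accelerometer data also matters in itself, because differential loss could bias the accelerometer outcome of a definitive trial. None of the stated Aim 1 indicators would show such a gap.

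The article gives reasons why the arms might differ. FFW participants are asked for at least 30 challenges, put at roughly 4 hours (Self-efficacy to comply). Their W2 payment is $25 for survey, monitoring and challenges together, against $10 in UC for survey and monitoring.

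**Working it through.** **Inputs.** From the article: 15 FFW + 15 UC = 30, which agrees with the target; participation red < 50%, green ≥ 70%; retention red < 40%, green ≥ 60%. The sample size rests on budget and precedent, so there is no power figure to reproduce. Simplification: all 30 consented participants are randomised, 15 to each arm. The article gives no arm-specific rates, so all those used below are assumptions.

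**Step 1: cut-offs as counts.**

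| Indicator | Pooled green | FFW arm alone red | FFW arm alone green |
|---|---|---|---|
| Participation | 0.70 × 30 = 21 or more | 7 or fewer (7/15 = 46.7%) | 11 or more (11/15 = 73.3%) |
| Retention | 0.60 × 30 = 18 or more | 5 or fewer (5/15 = 33.3%) | 9 or more (9/15 = 60.0%) |

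**Step 2: all outcomes with pooled green and FFW red.** Pairs are (FFW count, UC count), each out of 15.

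- Participation: (6, 15) and (7, 14), both 21/30 = 70.0%; (7, 15), 22/30 = 73.3%.
- Retention: (3, 15), (4, 14) and (5, 13), all 18/30 = 60.0%; (4, 15) and (5, 14), both 19/30 = 63.3%; (5, 15), 20/30 = 66.7%.

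UC must therefore reach at least 14/15 for participation or 13/15 for retention.

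**Step 3: how often.** Let F ~ Bin(15, p_F) and U ~ Bin(15, p_U) be independent. The event of interest is joint: P(F + U ≥ 21 and F ≤ 7) for participation, and P(F + U ≥ 18 and F ≤ 5) for retention.

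| Indicator | Assumed FFW / UC | Pooled green | FFW red | Both together |
|---|---|---|---|---|
| Participation | 40% / 90% | 33% | 79% | 14% |
| Participation | 60% / 80% | 59% | 21% | 2.2% |
| Participation | 65% / 75% | 59% | 11% | 0.6% |
| Participation | 70% / 70% | 59% | 5% | 0.1% |
| Retention | 30% / 90% | 59% | 72% | 32% |
| Retention | 35% / 85% | 59% | 56% | 20% |
| Retention | 50% / 70% | 58% | 15% | 1.3% |
| Retention | 60% / 60% | 58% | 3% | 0.1% |

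The milder mismatch, pooled green while FFW is not green, is commoner: 38% for participation at 60%/80% and 49% for retention at 40%/80%. Part of it is sampling noise, since it occurs 16% of the time for participation at 70%/70%.

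**Step 4: would a worse-arm light be better?** With both arms truly at 70% participation, the pooled light is green 59% and red 0.6% of the time. A light read from the worse arm is green 27% and red 10%. With both at 60%, the worse-arm light is red 38% of the time, against 10% pooled.

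**The case against.** The pooled rate has a sound purpose. Proposed study places all four aims in preparation for a definitive RCT, and Data analysis reads a green light as support for one. That trial needs usable data from both arms. Recruitment, eligibility and consent necessarily precede allocation, and the later rates continue the same funnel. This stands, and it is why the pooled rate should stay. It does not make the pooled rate an answer about use within FFW.

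A reader might infer that FFW participants will wear the monitors less. The document does not support a direction. The challenges add burden, but they end in week 6, before monitoring in weeks 8 and 12. The W2 payment is larger in FFW but is listed together with the challenges, and the W3 payment is $10 in both arms.

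A reader might also set 33% pooled green beside 79% FFW red and conclude that masking is the usual result. Those are separate probabilities. The joint figure is 14%, and in the same scenario the pooled light is not green 67% of the time. It also takes an assumed gap of 50 points; at gaps of 10 to 20 points the joint event is about 2% or less.

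Finally, reporting follow-up by arm is ordinary practice and may be planned in a document not shown. Nothing in the article rules it out. But the article does fix the formula, the denominator and the reading of the light, and the point is about those.

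**Conclusion.** The point holds in a limited form. At W2 and W3 the participation and retention lights do not isolate the arm that Aim 1 asks about, and a pooled green can coexist with an FFW rate that is red on the plan's own scale. With 15 per arm this happens at three count pairs for participation and six for retention, all with UC at 13/15 or better.

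Its probability depends wholly on assumed rates: 14% and 32% in the extreme scenarios, about 2% or less for gaps of 10 to 20 points, and about 0.1% when the arms are alike. The stronger conclusion, that the pooled lights are invalid or likely to mislead, is not supported. W1 is not affected, because its monitoring precedes FFW access. The change is worth making because it is cheap and lets the study speak to its own aim and to differential loss of accelerometer data.

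**What to change.** In the Participation rates and Retention rates definitions and in Table 2:

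1. Keep the pooled rates and their lights, and keep W1 participation pooled only.
2. At W2 and W3, also compute participation and retention for FFW and UC separately. Use the number randomised to that arm as denominator, since someone who consents but does not finish the W1 survey has no arm.
3. Report the between-arm difference with its 95% CI, in line with the general statement on intervals under Data analysis.
4. State that Aim 1 is not read as green for use within FFW when the FFW rate is below the existing lower threshold (50% participation, 40% retention).

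Do not base the light on the worse arm. Taking the smaller of two proportions, each from 15 people, at unchanged thresholds biases the light downward even when the arms are equal.

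The cost is some wording and a few percentages from data already being collected. The drawbacks are that each arm rate moves in steps of 1/15 = 6.7 points and is imprecise, and that the conclusion may be less favourable. With both arms truly at 70% participation, the FFW arm alone would still be red 5% of the time, so the arm rate should be read with its interval.
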